## Abstract

**Methods::**

A randomized, double-blind, placebo-controlled parallel trial will be conducted to assess 20 patients with chronic upper body pruritus for 3 months who have been diagnosed with allergic atopic dermatitis or seborrheic dermatitis. The patients will be randomly allocated to either the placebo-control (n = 10) or treatment (n = 10) group. The total study period will be 8 weeks (i.e., administration of *Sopoongsan* or placebo drugs for 4 wk and follow-up for 4 wk). Participants will be allowed to receive external treatment, except for antipruritic medications administered orally, throughout the study period. The primary outcome measure will be the numeric rating scale results for itching, whereas the secondary outcome measures will be questionnaire survey (Dermatological Life Quality Index and Epworth Sleepiness Scale) findings and the immune response index, including interferon gamma, interleukin-4, immunoglobulin E, thymic stromal lymphopoietic protein, and histamine, to investigate the biological mechanisms underlying chronic pruritus.

**Discussion and Conclusions::**

We expect that the results of this study will provide important clinical evidence regarding the effectiveness of *Sopoongsan* on itching symptoms, quality of life, sleep disturbance, and changes in the immune response. The findings will help elucidate the mechanism underlying the therapeutic effect of *Sopoongsan* for chronic pruritus and lay the foundation for further studies in this area.

## 1. Introduction

Chronic pruritus is described as an irritating sensation that elicits a desire to scratch and persists for more than 6 weeks. Scratching can aggravate dermal conditions, cause emotional disturbance and sleep loss, and decrease the quality of life.^[1,2]^ The cause of pruritus can be dermatological (e.g., atopic eczema and psoriasis), systemic (kidney failure and liver cirrhosis), neuropathic (notalgia paresthetica), or psychogenic. Chronic pruritus is widespread, with a high estimated prevalence of 15%,^[3]^ and is very difficult to treat.^[4]^ There are no approved pharmacological drugs for the treatment of chronic pruritus.^[5]^ Sedating antihistamines are commonly used as first-line pharmacological therapy for pruritus, but often have only modest efficacy in clinical practice.^[1]^ Therefore, complementary treatment strategies that overcome these limitations are required; however, randomized and controlled trial reports on various pharmacological and nonpharmacological treatments for chronic pruritus are scarce.

*Sopoongsan* is a traditional medicine that is widely used in clinical practice to improve skin diseases based on a nationwide study.^[6–9]^
*Sopoongsan*, called Xiao-feng-san in Chinese, has been reported as the most commonly used traditional medicine for dampness and heat-based pruritus in atopic dermatitis and urticaria; it has also been shown to exert anti-inflammatory, antioxidation, and antiallergic effects.^[7–9]^
*Sopoongsan* is divided into two prescriptions, depending on the source. The first prescription is Waikezhengzong, which contains *Saposhnikovia divaricata*, *Atractylodes lancea*, *Schizonepeta tenuifolia*, *Arctium lappa*, *Glycyrrhiza uralensis*, *Rehmannia glutinosa*, *Gypsum fibrosum*, *Clematis armandii*, *Cryptotympana pustulata*, *Linum usitatissimum*, *Sophora flavescens*, *Angelica sinensis*, and *Anemarrhena asphodeloides*, and is highly effective against dampness and heat-based atopic dermatitis, urticaria, and eczema. As a result of administering *Sopoongsan* to patients with chronic urticaria for 28 days in a randomized controlled trial (RCT), an improvement in patients’ itching symptoms and sleep status and a reduction in serum interferon-gamma (IFN-γ) levels were observed. After administering *Sopoongsan* for 8 weeks in patients with atopic dermatitis, the patients showed an improvement in atopic lesion scores, along with an improvement in itching and sleep status.^[10,11]^ The other prescription is composed of *Notopterygium incisum*, *Pericarpium Citri Reticulatae*, *Cryptotympana pustulata*, *Schizonepeta tenuifolia*, *Smilax china*, *Bombyx batryticatus*, *Saposhnikovia divaricata*, *Agastache rugosa O. Ktze.*, *Magnolia officinalis Rehd*, *Glycyrrhiza uralensis*, *Panax ginseng*, and *Ligusticum chuanxiong Hort* from Dong-uibogam in the Republic of Korea. In contrast to the former, it is more commonly used for dry lesions rather than Waikezhengzong *Sopoongsan*, as it strengthens the vital force and improves the circulation of fluid qi. In animal models in which histamine and ear swelling have been induced, *Sopoongsan* has been confirmed to inhibit mast cell degranulation and histamine secretion, reduce ear swelling, and decrease the levels of nuclear factor kappa B, tumor necrosis factor-alpha, interleukin (IL)-8, and IL-6. However, to date, clinical studies on the effectiveness of *Sopoongsan* used in the Republic of Korea for patients with dermatological diseases have been limited.

The biological mechanisms underlying chronic pruritus are complex and multifactorial.^[1]^ The itch-sensitive neurons originating in the skin are stimulated by several pruritogens, including histamine, immune cells, keratinocytes, and nerves.^[4]^ Histamine activates neurons via the histamine receptor 1, leading to the opening of the heat- and capsaicin-gated transient receptor potential (TRP) channel. TRP channels are key transduction ion channels on the plasma membrane that exacerbate the excitation of neurons and promote itching. Moreover, other non-histaminergic endogenous pruritogens are released from keratinocytes, such as cytokine thymic stromal lymphopoietic protein (TSLP), which activates neurons via the TSLP receptor leading to the opening of TRP ankyrin 1 channels. Activating TRP leads to depolarization, action potential firing, and transmission of itch-neuronal signals from the periphery to the central nervous system.^[4]^ The itch signal is transmitted to areas of the brain that are involved in sensation, evaluative processes, emotion, reward, and memory.^[1]^ Collectively, the analysis of pruritus-related immune cytokines may help elucidate the therapeutic biological mechanisms by which *Sopoongsan* can benefit patients with chronic pruritus. Nonetheless, RCTs investigating the *Sopoongsan*-induced changes in the immune response in serum samples of patients with chronic pruritus are limited.

In this study, we report our study design and plans for evaluating the effectiveness of *Sopoongsan* in patients with chronic pruritus and the feasibility for analyzing data collected during the whole process of the trial. Furthermore, we will elucidate the mechanism underlying the effectiveness of *Sopoongsan* in patients with chronic pruritus by measuring the levels of immune-related cytokines. The specific objectives of the study include the verification of research feasibility to assess the effectiveness of *Sopoongsan* for improving skin itching in patients with chronic upper body pruritus and the investigation of the possibility of immune indicators as therapeutic response biomarkers in response to *Sopoongsan* for skin pruritus.

## 2. Methods

### 2.1. Study design and setting

This clinical study will be a randomized placebo-controlled trial investigating the effectiveness of *Sopoongsan* in the treatment of upper body pruritus in patients with allergic atopic or seborrheic dermatitis. *Sopoongsan* or placebo will be administered orally three times daily for 4 weeks, with a follow-up of 4 weeks. A flow chart describing the clinical study design is illustrated in Figure 1. The effect of *Sopoongsan* on itching will be assessed by improvements in itching symptoms, Dermatology Life Quality Index, presence of sleep disorders due to itching, and changes in immune indicators in the blood. The study setting and site of data collection will be the Clinical Trial Center at the Kyung Hee Korean Medical Hospital, Kyung Hee University, in the Republic of Korea.

**Figure 1. F1:**
[figure not shown]
The study design flowchart showing details of the randomized controlled trial.

### 2.2. Participant recruitment

A total of 20 participants with upper body pruritus will be recruited through posters placed in the hospital and community, local newspapers, and subway advertisements from November 2022 to December 2023. The participants who meet the eligibility criteria (Table 1) will receive information regarding the clinical study during a consultation with the coordinator and provide written informed consent for their participation in this study. Subsequently, all participations will be randomly allocated to either the treatment or control group.

**Table 1 T1:** Patient eligibility criteria.

Inclusion criteria
(1) Patients aged ≥ 19 years (2) NRS score of ≥ 3 for upper body pruritus (3) Pruritus of ≥ 3 months (4) Diagnosis: allergic atopic or seborrheic dermatitis (5) Provided voluntary written informed consent to participate in this clinical study
Exclusion criteria
(1) NRS score of ≥ 7 for upper body pruritus (2) History of taking oral adrenal corticosteroids (steroids) or immunosuppressants for skin itching within the last 4 weeks (3) Skin diseases caused by bacterial or viral infections (4) Clinical abnormality of liver and renal function tests (i.e., ALT, AST, ALP) ≥ 2 times the upper limit of normal or creatinine > 2.0 mg/dL at screening (5) Severe acute cardiovascular disease (i.e., heart failure, myocardial infarction, stroke, hypertension, or diabetes) (6) Serious conditions of hyperlipidemia, anemia, active pulmonary tuberculosis, thyroid disease, and other infectious and systemic diseases (7) Past or present malignant tumors (8) Antipsychotic drug treatment within 2 months before screening test (9) History of acute or chronic pancreatitis or gastrointestinal surgery (except for simple appendix surgery or hernia surgery) (10) Genetic problems such as galactose intolerance, Lapp lactase deficiency, or glucose-galactose malabsorption (11) History of hypersensitivity reactions to the constituents of the clinical trial treatments (12) History of drug or alcohol abuse (13) Pregnant and lactating women or in case or accepting the implementation of an appropriate contraceptive method among women of pregnant potential who are likely to become pregnant (except for women who have undergone sterilization) (14) Plan to participate in other clinical trials after enrollment in this clinical trial, or who have participated in other clinical trials during the 30 days prior to registration in this clinical trial (15) Inappropriate patients as considered by the investigator for other reasons

ALP = alkaline phosphatase, ALT = alanine aminotransferase, AST = aspartate aminotransferase, NRS = numeric rating scale.

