### 2.4. Interventions

All participants in both groups will be allowed to receive external treatment, except for antipruritic medications administered orally and herbal medicine treatment. All participants will orally take either *Sopoongsan* or placebo drugs three times daily, which will be packed in opaque sachets, in granular form. Discontinuation of the intervention by participants may occur because of withdrawal of informed consent by participants or their legal representatives, violation of the eligibility criteria during the clinical trial, occurrence of adverse events, and < 70% compliance with the medication criteria. Medication adherence (number of medicines received/number of medicines to be received) will be assessed by the clinical research coordinator every time the participants visit the clinic.

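### Exclusion criterion 13 is garbled and, as printed, makes accepting contraception a ground for exclusion, which does not fit the rest of the same criterion

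*Protocol article*

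**What the plan says.** Section 2.2 makes Table 1 the entry gate: people who satisfy it are informed about the study, give consent and are then randomised. Under the exclusion heading of that table, item 13 opens "Pregnant and lactating women or in case or accepting the implementation of an appropriate contraceptive method among women of pregnant potential". Its limb on contraception, from the verb onward, reads "accepting the implementation of an appropriate contraceptive method among women of pregnant potential who are likely to become pregnant", and the item closes with a bracketed exemption, "except for women who have undergone sterilization".

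The criteria also matter after enrolment. Section 2.4 names "violation of the eligibility criteria during the clinical trial" among the reasons for which the intervention may be discontinued.

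**The concern.** An item in an exclusion list describes who may not enter. Item 13 describes women of childbearing potential as accepting contraception, so on its face acceptance is what disqualifies them. A rule that begins by keeping out pregnant and lactating women would be expected to point the other way.

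The matter at stake is participant safety. If the printed sentence were applied literally, women who could conceive and do not accept contraception would be eligible to take a 12-ingredient oral herbal preparation for 4 weeks, and women who do accept it would be turned away. Through Section 2.4, a participant who took up contraception during the trial would also fall under an exclusion.

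**Working it through.** No arithmetic applies. The check is to read item 13 as printed, compare its parts, and look for any other text that governs the same women.

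**1. Literal reading, group by group.**

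| Woman's status | Effect of item 13 as printed |
|---|---|
| Pregnant or lactating | Excluded |
| Childbearing potential, not sterilised, accepts contraception | Excluded |
| Childbearing potential, not sterilised, does not accept contraception | Not excluded by this item |
| Sterilised | Exempt |

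**2. Comparison of the parts.** The first limb (pregnant and lactating women) shows an aim of avoiding exposure in pregnancy. The second limb, read literally, removes the women who take precautions against pregnancy and keeps those who do not. The exemption frees women who have been sterilised. That has a clear purpose if the second limb is aimed at women who might conceive, and almost none if it is aimed at women who accept contraception. The parts agree only if a negation is missing from the second limb.

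**3. State of the sentence.** The link between the two limbs, visible in "Pregnant and lactating women or in case or accepting the implementation of an appropriate contraceptive method among women of pregnant potential", does not parse. Words have been lost or mistranslated at exactly the place where a negation would stand.

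**4. Search for a correcting rule.** The five inclusion criteria cover age, itch score, duration, diagnosis and consent; the last two read "4) Diagnosis: allergic atopic or seborrheic dermatitis (5) Provided voluntary written informed consent to participate in this clinical study". None mentions contraception. The only other exclusion that could reach these women is item 15, "Inappropriate patients as considered by the investigator for other reasons", which is general discretion and not a contraception rule. No other section of the article states a pregnancy or contraception requirement. The printed error therefore stands uncorrected within the document.

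**The case against.** The strongest reply is that this is a broken sentence and not a reversed rule. The wording is so visibly damaged, and the sterilisation exemption so clearly signals the intent, that screening staff would be unlikely to apply it literally. They would also work from the approved protocol, version 1.3 according to Section 2.9, and not from a journal table. Pregnant and lactating women are excluded on any reading. The mismatch with the exemption is also an oddity more than a strict logical contradiction: one can exempt sterilised women from a literal exclusion for accepting contraception, even though doing so achieves nothing.

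Most of this stands. It makes a drafting or translation error the likely explanation and misapplication at the site unproven. It does not make the printed text right. The article does more than leave the rule to a fuller document: it states a rule, and states it in the wrong direction for its own other parts. That version 1.3 may differ is a reason to compare the two.

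A reader might go further and infer that the investigators chose to admit women who decline contraception, or that such women have been exposed. The documents support neither. A reader might also infer that the feasibility results are distorted. Section 2.5.2.4 counts those who met the inclusion criteria, whereas item 13 is an exclusion. Nothing shows that exclusions enter that proportion or that the item was applied literally, so that inference is not supported either.

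**Conclusion.** The point holds as a wording defect in a safety-related eligibility criterion. As printed, item 13 excludes women of childbearing potential who accept contraception, leaves those who do not accept it eligible, and does not fit its own first limb or its own exemption. No other text in the article repairs it.

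The practical effect is conditional. Only on a literal reading does eligibility reverse for non-sterilised women of childbearing potential. How many of the 20 participants this could concern is unknown, since the article gives no expected sex or age distribution. The conclusion assumes that the printed words are as the authors submitted them, and it makes no claim about the content of version 1.3 or about practice at the site. The sample size of 10 per group and the planned analysis are unaffected. The point still warrants correction because the possible consequence concerns participant safety and the remedy is small.

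**What to change.** Compare item 13 in the article with the approved protocol version 1.3 and with the screening form. Correct the printed wording so that its three parts (pregnant and lactating women, women of childbearing potential, sterilised women) agree with one another and with the approved text. What the contraception requirement should be is for the sponsor and the IRB to confirm from that text; this point does not propose one.

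If version 1.3 or the screening form carries the same wording, correct it there too by the amendment route in Section 2.9, and check the screening log for how women of childbearing potential were classified. If both are already consistent, a correction to the article is enough and no log review is needed.

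The cost is one line of text and, in the worse case, a review of the screening log of a 20-participant trial. The design, sample size and analysis do not change.

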### 2.3. Randomization and blinding

The allocation of eligible patients to the control or *Sopoongsan* treatment group at a 1:1 ratio will be performed by an independent statistician using computer-generated block randomization. Each participant will be selected via systematic sampling and receive an identification code enclosed in an opaque envelope. This will be a double-blind study because the participants, researchers, and assessors collecting the data will be blinded to group assignment. If the blinding was disrupted such as in a medical emergency, the principal investigator will hold a researchers’ meeting to decide if unblinding is required. In this case, the unblinding will be informed to the institutional review board (IRB) within 24 h. The enrollment of participants, allocation sequence, and assignment of participants will be the responsibility of the Clinical Trial Center at the Kyung Hee Korean Medical Hospital, Kyung Hee University.

### 2.4. Interventions

All participants in both groups will be allowed to receive external treatment, except for antipruritic medications administered orally and herbal medicine treatment. All participants will orally take either *Sopoongsan* or placebo drugs three times daily, which will be packed in opaque sachets, in granular form. Discontinuation of the intervention by participants may occur because of withdrawal of informed consent by participants or their legal representatives, violation of the eligibility criteria during the clinical trial, occurrence of adverse events, and < 70% compliance with the medication criteria. Medication adherence (number of medicines received/number of medicines to be received) will be assessed by the clinical research coordinator every time the participants visit the clinic.

#### 2.4.1. Treatment group: Sopoongsan.

The treatment group will receive *Sopoongsan*, which contains the following 12 dried medicinal herbs: *Notopterygium incisum*, *Pericarpium Citri Reticulatae*, *Cryptotympana pustulata*, *Schizonepeta tenuifolia*, *Smilax china*, *Bombyx batryticatus*, *Saposhnikovia divaricata*, *Agastache rugosa O. Ktze.*, *Magnolia officinalis Rehd*, *Glycyrrhiza uralensis*, *Panax ginseng*, and *Ligusticum chuanxiong Hort*. The formula will be supplied by the manufacturer of the National Institute for Korean Medicine Development (Republic of Korea) and is manufactured in compliance with Good Manufacturing Practice under the Ministry of Food and Drug Safety guidelines. The final form of *Sopoongsan* is granular.

#### 2.4.2. Control group: placebo.

The control group will be administered a placebo formulation containing lactose, starch, and caramel coloring, which will be manufactured using the same process and by the same manufacturer as those for *Sopoongsan.*

### 2.5. Outcome measures

To evaluate the effect of *Sopoongsan* on skin itching, the intensity of pruritus, as assessed using a numeric rating scale (NRS), will be the primary outcome. The secondary outcome measures will include findings from instruments that evaluate the quality of life, sleep impairment, and changes in the immune response. The schedule for outcome measurements is illustrated in Table 2.

**Table 2 T2:** Schedule for enrollment, clinical outcomes, and safety assessment.

Period	Screening	Treatment			Follow-up*
Visit	Screening	Visit 1	Visit 2	Visit 3	Visit 4
Week	0 week (baseline)	1 week	2 weeks	4 weeks	8 weeks
Provide informed consent	**○**				
Identification of inclusion and exclusion criteria	**○**				
Demographics	**○**				
Medical and disease history	**○**				
Clinical laboratory examination	**○**			**○**	
Vital signs	**○**			**○**	
NRS	**○**	**○**	**○**	**○**	**○**
DLQI		**○**	**○**	**○**	**○**
ESS		**○**	**○**	**○**	**○**
Blood collection for immune analysis	**○**			**○**	
Supply of drug for clinical trial		**○**	**○**		
Medication compliance			**○**	**○**	**○**
Identification of adverse reaction(s)			**○**	**○**	**○**
Identification of concomitant drug change		**○**	**○**	**○**	

DLQI = Dermatological Life Quality Index, ESS = Epworth sleep scale, NRS = numeric rating scale.

* Follow-up by phone interviews.

#### 2.5..1. Primary outcome: intensity of pruritus.

The NRS is a numerical rating scale anchored at 0 and 10 that is marked by patients to indicate their intensity of itch. It has been validated in large-scale studies for chronic pruritus.^[12]^ The intensity of pruritus, as assessed using the NRS, will be the primary outcome. The measurement will be performed at baseline (visit 1), 2 weeks, and 4 weeks during and after treatment (visits 2 and 3) and at follow-up after 4 weeks (visit 4) for both groups.

#### 2.5.2. Secondary outcomes.

##### 2.5.2.1. Quality of life.

Chronic pruritus can greatly reduce the patients’ quality of life. The Dermatological Life Quality Index , an instrument for both pruritus and other dermatological conditions, is widely used and validated.^[12]^ The measurement will be performed at baseline (visit 1), 2 weeks, and 4 weeks during and after treatment (visits 2 and 3) and at follow-up after 4 weeks (visit 4) for both groups.

